#### Interim Analysis

# An independent DSMB will evaluate safety after the first 30 patients have reached treatment weeks 2 and 12.

## Sample Size

This is a pilot trial with the viral kinetic response and SVR measured as described above, during the first 12 weeks of therapy as primary endpoint with the aim of investigating the feasibility and safety of “loading” and “priming” dosing of ribavirin in conjunction with PEG-IFN for chronic HCV genotyp 1. To demonstrate an increase in the reduction of HCV RNA from day 0 to 3 from 0.9 log10 IU/mL in Group C (Standard-of-Care) to 1.4 log10 IU/mL in Group A or B or an increase in the reduction of HCV RNA from day 7 to 28 from 0.4 log10 IU/mL/week in Group C (Standard-of-Care) to 0.6 log10 IU/mL/week in Group A or B the study requires at least 35 patients per study arm. The statistical power (chance) for the study to detect a superior effect in Group A or B as compared to C is 80%. Statistical sample-size calculation is based on z-test for differences between proportions and is one-sided with a significance level of 5%.

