| TRIAL DESIGN | Multicenter, randomized, open-label, parallel group pilot study.  Randomization to the three treatment arms A, B and C will be stratified by gender, age above or below 40 years, and presence of liver cirrhosis/non-cirrhosis (as evaluated by the Gothenburg University Cirrhosis Index (GUCI) 1.0). | | |
| DISCONTINUATION SCHEME | Treatment will be stopped in patients having a decline of HCV-RNA less than 2-log10 after 12 weeks or detectable HCV-RNA after 24 weeks of study treatment as measured by Roche COBAS AmpliPrep/COBAS TaqMan HCV Test (≤15 IU/mL) | | |
| NUMBER OF SUBJECTS | Total of 105 patients, 35 per treatment group. | | |
| TARGET POPULATION | Men and women >18 years old with CHC genotype 1 will be enrolled in this study. Patients must have quantifiable HCV-RNA, and must have compensated liver disease (Child-Pugh Grade A). Liver biopsies and/or FibroScan evaluations are encouraged especially for patients with a Gothenburg University Cirrhosis Index (GUCI, a cirrhosis index calculated by (normalized AST x PK-INR x 100) / Platelet count (x 109/L)) 1.0, but not mandatory. Patients with other forms of liver disease, human immunodeficiency virus (HIV) infection, hepatocellular carcinoma, anemia, pre-existing severe depression or other psychiatric disease, significant cardiac disease, renal disease, seizure disorders, or severe retinopathy, or previously treated with interferon/ peg-interferon with or without ribavirin are excluded. | | |

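### The 80% power at 35 per arm is attributed to a z-test for proportions, but the planning effects are log10 HCV-RNA declines and no SD is given, so the figure cannot be reproduced

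*Protocol*

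**What the plan says.** Protocol section 9.3 (Sample Size) sets two planning effects. The first-phase effect is given as "reduction of HCV RNA from day 0 to 3 from 0.9 log10 IU/mL in Group C (Standard-of-Care) to 1.4 log10 IU/mL in Group A or" (the sentence then names the other experimental arm). For the second phase (day 7 to 28) it plans on an increase "from 0.4 log10 IU/mL/week in Group C (Standard-of-Care) to 0.6 log10 IU/mL/week in Group A or B". It concludes that "the study requires at least 35 patients per study arm" and adds: "The statistical power (chance) for the study to detect a superior effect in Group A or B as compared to C is 80" percent. The method sentence is: "Statistical sample-size calculation is based on z-test for differences between proportions and is one-sided with a significance level of 5" percent. The synopsis (Statistical Analyses) carries the same text.

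The primary variable in sections 6.1 and 9.1.1 is the decline in HCV-RNA over the first 12 weeks. The responder rates (VRVR, RVR, cEVR, pEVR) are secondary (sections 6.2 and 9.1.2). The synopsis entry on number of subjects reads: "Total of 105 patients, 35 per treatment group". Section 3.2 repeats this, so the number enrolled equals the stated minimum. The protocol gives no SD, variance or responder proportion for the calculation.

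**The concern.** The named test does not fit the quantities it is said to have been applied to. A z-test for proportions needs two numbers between 0 and 1, and it takes its variance from those numbers. The stated effects are declines in log10 units, one of them above 1, and for declines the variance must be supplied as an SD. None is supplied.

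This paragraph is the protocol's only justification for N and its only statement of power. The trial calls itself a pilot, but its synopsis objective is to demonstrate efficacy and section 9.3 claims power to detect superiority. A power figure used in that way should be traceable to its inputs. As written, a reader cannot tell what difference 35 per arm was able to detect at 80% power.

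**Working it through.** **Inputs from the protocol (section 9.3 and synopsis).** One-sided alpha 0.05, so z = 1.645. Power 80%, so z = 0.842. n = 35 per arm. Differences: 1.4 − 0.9 = 0.5 log10 IU/mL and 0.6 − 0.4 = 0.2 log10 IU/mL/week.

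**Step 1: try to reproduce 35 by the stated method.**
- 0.9 vs 1.4 cannot be entered, because 1.4 is not a proportion.
- 0.4 vs 0.6 read as proportions:
  - Unpooled: n = (1.645 + 0.842)² × (0.4×0.6 + 0.6×0.4) / 0.2² = 74.2 per arm.
  - Pooled: n = [1.645 × √(2×0.5×0.5) + 0.842 × √(0.24 + 0.24)]² / 0.2² = 76.2 per arm.
  - At n = 35 these inputs give 51.2% (pooled) or 52.5% (unpooled).
- Other variants do not reach 35 either (pooled, rounded up). 0.4 vs 0.6 needs 86 one-sided with continuity correction, 97 two-sided, and 107 two-sided with correction. Converting the log declines to the fraction of virus cleared (1 − 10^−x) gives 0.874 vs 0.960, needing 126 one-sided, and 0.602 vs 0.749, needing 125.

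No proportions calculation tried yields 35.

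**Step 2: the method that fits the endpoint, solved backwards.** For a two-sample comparison of means, power = Φ(Δ/SD × √(n/2) − 1.645). Setting this to 80% gives SD = Δ × √(35/2) / (1.645 + 0.842).
- First phase: 0.5 × 4.183 / 2.486 = 0.841. The noncentral t gives 0.833.
- Second phase: 0.2 × 4.183 / 2.486 = 0.336. The noncentral t gives 0.333.

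These are upper limits: a smaller SD gives more than 80%. Both correspond to the same standardised difference, 0.5/0.841 = 0.2/0.336 ≈ 0.594.

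**Step 3: power at 35 per arm under assumed SDs.** The SDs below are assumptions; the protocol states none.

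| Phase | Assumed SD | Power, normal | Power, noncentral t |
| --- | --- | --- | --- |
| First (Δ 0.5) | 0.7 | 91.0% | 90.6% |
| First | 1.0 | 67.2% | 66.5% |
| First | 1.2 | 53.9% | 53.2% |
| Second (Δ 0.2) | 0.3 | 87.4% | 86.8% |
| Second | 0.4 | 67.2% | 66.5% |
| Second | 0.5 | 51.1% | 50.5% |

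**Step 4: what the 80% refers to.** The wording "The statistical power (chance) for the study to detect a superior effect in Group A or B as compared to C is 80" percent can mean each comparison with C, or at least one of the two succeeding. Under the second reading, assume the same true effect in A and B, each tested at one-sided 5%, and correlation 0.5 through the shared control. Then 80% is reached at SDs up to about 1.04 and 0.41.

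**Step 5: evaluable patients.** Hold the SD at the value that gives exactly 80% with 35 per arm. Then 34 evaluable per arm gives about 79%, and 31 per arm about 76%. The figure 31 is an assumption for illustration; the protocol gives no loss rate.

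**The case against.** The strongest reply is that this is only a labelling slip. Both phases imply the same standardised difference at n = 35, which is what a two-means calculation could produce, and the trial calls itself a pilot aimed at feasibility and safety. That reply may be right about the origin of the number, but the protocol does not say so. Even if it is right, the method sentence is wrong and the input that decides the power is undisclosed. A separate SAP would not correct a wrong test named in the protocol as the basis for N.

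The reply does limit the point, and several stronger readings are not supported:
- A reader might infer that 35 was derived from a proportions test. Step 1 shows the opposite: no such calculation tried gives 35.
- A reader might take 51–53% as the trial's power. It is not. It treats rates in log10 IU/mL/week as proportions, and shows only that the label fails.
- A reader might conclude that the trial is underpowered. An SD below the limits in step 2, or the at-least-one reading in step 4, would leave power at or above 80%.
- A reader might say that a null result could not be interpreted. It could, from the observed difference and its confidence interval, which use the observed SD. The missing planning SD weakens the justification of N, not the later inference.
- The absence of a margin above 35 is real but small: the planning endpoints end at day 3 and day 28, and losing one patient per arm costs about one percentage point.

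**Conclusion.** The point holds in a limited form. Section 9.3 and the synopsis name a method that cannot accept one planning effect and does not give 35 for the other, so the calculation is misdescribed and the stated 80% is not reproducible. With the method that fits the endpoint, and one pairwise comparison at one-sided 5%, 80% at 35 per arm requires an SD of at most about 0.83–0.84 log10 IU/mL and 0.333–0.336 log10 IU/mL/week. Neither value is in the protocol.

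Under the assumed SDs, power is about 91%, 66–67% and 53–54% for the first phase, and about 87%, 66–67% and 50–51% for the second. The direction of any error is therefore unknown. The conclusion rests on reading the stated declines as group means. The protocol does not use that word in the sample-size text, but it is the natural reading.

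**What to change.** In both section 9.3 and the synopsis:
1. Replace the proportions sentence with a two-sample comparison of mean log10 HCV-RNA decline.
2. State the assumed SD and its source for each phase.
3. Say whether the 80% applies to each comparison with C or to at least one of A and B.
4. Restate the power at 35 per arm and at a stated, assumed evaluable number.

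N stays at 105. No analysis model needs to be prescribed here, since that may sit in the SAP. In particular, covariate adjustment for day-0 HCV-RNA should not be added as part of this correction: in Group B, day 0 follows four weeks of randomised ribavirin (sections 3.1 and 5.3.1), so in that arm it is a post-randomisation value.

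The cost is rewording two paragraphs, with no extra patients, visits or assays. The downside is that the restated power may be less favourable than 80%.

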# Data Quality Assurance

Accurate and reliable data collection will be assured by the investigator. The data collected will be entered into a computer database and subject to quality assurance procedures as dictated by the steering committee. The data collected will be archived for at least 10 years after the termination of the study.

# Publication

Presentations of the study results at conferences and publications in journals will be prepared by the steering committee.

Appendix 1 Child-Pugh Classification of Severity of Liver Disease

|  | **Points Scored for Increasing Abnormality** | | |
| --- | --- | --- | --- |
| **Clinical and Biochemical Measurements** | **1** | **2** | **3** |
| Encephalopathy (grade)a | None | 1 or 2 | 3 or 4 |
| Ascitesb | Absent | Slight | Moderate |
| Bilirubin (mg per 100 mL)  SI unit= (µmol/l) | < 2  <34 | 2 – 3  34-51 | >3  >51 |
| Albumin (g per 100 mL) | > 3.5 | 2.8 – 3.5 | < 2.8 |
| INR | < 1.7 | 1.7-2.3 | > 2.3 |

a According to grading of Trey, Burns and Saunders (1996)

b As determined by physical examination alone

1, 2 or 3 points are scored for increasing abnormality of each of the 5 parameters measured.

Grade **A**: Total score of 5 or 6

Grade **B**: Total score of 7 to 9

Grade **C**: Total score of 10 to 15

Appendix 2 PEGASYS Dose Adjustment Guidelines

Specific dose adjustment guidelines for PEGASYS are provided below for post-treatment, neutropenia, thrombocytopenia, elevated serum ALT activities, and depression. It should be kept in mind that other responses by an investigator, in accordance with local guidelines, may be more appropriate, and that an investigator does not have to abide by the dose adjustment guidelines listed below. For other adverse effects considered to be related to PEGASYS, including laboratory abnor­malities, adverse events, and vital sign changes, investigators should utilize the table below labeled “PEGASYS General Dose Reduction Guidelines.” When practicable, abnormal laboratory results should be confirmed as soon as possible following notification of the investigator. If appropriate, downward adjustments in one level decrements (see section 7.3.1) should be considered. The lowest dose of PEGASYS that should be administered is 45 µg. For laboratory and vital signs abnormalities, “severe” is defined as any value requiring intervention, further work-up, or more frequent follow-up.

PEGASYS General Dose Reduction Guidelines

| **Number of Dose Reduction Levels (see Section 7.3.1)** | | | | | |
| --- | --- | --- | --- | --- | --- |
| **Mild** | **Moderate**  **Limited** | **Moderate**  **Persistent** | **Severe**  **Limited** | **Severe**  **Persistent** | **Life-Threatening** |
| 0 | 0 | 0-1 | 0-1 | 1-2 | Stop Drug |

Dose Adjustments for Low Absolute Neutrophil Counts

| **ANC** | **PEGASYS Dose Reduction** |
| --- | --- |
| < 750 cells/mm3 | 135 µg |
| < 500 cells/mm3 | Withhold treatment until ANC returns to >1000 cells/mm3. Resume treatment at 90 µg and monitor ANC |

Dose Adjustments for Low Platelet Counts

| **Platelet Count** | **PEGASYS Dose Reduction** |
| --- | --- |
| < 50.000 cells/mm3 | 90 µg |
| < 25.000 cells/mm3 | Withhold treatment |

**Appendix 2: PEGASYS Dose Adjustment Guidelines *(Cont.)***

**Dose Adjustments for Elevated Serum ALT**

Fluctuations in abnormalities of liver function tests are common in patients with chronic hepatitis C. As with other alfa interferons, increases in ALT levels above baseline (BL) have been observed in patients treated with PEGASYS, including patients with a virological response.

In patients with progressive ALT increases above baseline, the patient should be closely monitored and if necessary the dose of PEGASYS should be reduced to 135 µg. If ALT increases are progressive despite dose reduction, or accompanied by increased bilirubin or evidence of hepatic decompensation, therapy should be immediately discontinued.

**Dose Adjustments for Depression**

**The responsible physician may consider antidepressants more appropriate than dose reductions.**

| **Depression Severity** | **Initial Management (4-8 weeks)** | | **Depression** | | |
| --- | --- | --- | --- | --- | --- |
| **Dose Modification** | **Visit Schedule** | **Remains Stable** | **Improves** | **Worsens** |
| Mild | No change | Evaluate once weekly by visit and/or phone | Continue weekly visit schedule | Resume normal visit schedule | (See moderate or severe depression) |
| Moderate | Decrease PEGASYS dose to 135 µg (in some cases dose reduction to 90 µg may be needed) | Evaluate once weekly (office visit at least every other week) | Consider psychiatric consultation. Continue reduced dosing | If symptoms improve and are stable for 4 weeks, may resume normal visit schedule. Continue reduced dosing or return to normal dose | (See severe depression) |
| Severe | Discontinue PEGASYS permanently | Obtain immediate psychiatric consultation | Psychiatric therapy necessary | | |

**Appendix 3: COPEGUS Intended Dose and Dose Adjustment Guidelines**

| Group A: Intended Ribavirin Dosing | | |
| --- | --- | --- |
| Weight | Ribavirin dose day 0 – day 14* | Ribavirin dose day 15 -  End of Treatment** |
| 45-60 kg | 1600 mg | 800 mg |
| 61-75 kg | 2000 mg | 1000 mg |
| 76-90 kg | 2400 mg | 1200 mg |
| 91-105 kg | 2800 mg | 1400 mg |
| *Dose given TID. **Ribavirin concentration measured on treatment day 28. Dose | | |
| adjustments will be made at the discretion of the treating physician with the goal of | | |
| achieving ≥ 2.5 mg/L (10.25 μmol/L). A new ribavirin concentration is recommended | | |
| after an additional period of 4 weeks if the ribavirin dose is adjusted as above. | | |

| Group B and C: Intended Ribavirin Dosing |  |
| --- | --- |
| Weight | Ribavirin dose day 0 –  End of Treatment a,b |
| 45-60 kg | 800 mg |
| 61-75 kg | 1000 mg |
| 76-90 kg | 1200 mg |
| 91-105 kg | 1400 mg |
| aNo ribavirin concentrations will be measured while on treatment for group C.  bGroup B will receive 4 weeks of priming with ribavirin without PEG-IFN. | |

If the ribavirin concentration is below the target 2.5 mg/L (10.25 μmol/L) 28 days after the initiation of ribavirin, the dose of ribavirin should be increased as soon as possible preferably within 2 weeks of measuring the ribavirin concentration if the patient tolerates. The new recommended dose is the previously given dose divided by the concentration of ribavirin measured multiplied by the target concentration, i.e. 2.5 mg/L (10.25 μmol/L) as suggested in the table below. In the event of an increase in ribavirin dosing in Groups A (“Loading”) and B (“Priming”), a new local ribavirin concentration should be evaluated after 4 weeks.

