# OBJECTIVES OF The STUDY

## Primary Objective

To evaluate the efficacy of (A) 2 weeks of high dose of ribavirin (“loading”, ≥26 mg/kg/day for 14 days followed by ≥13 mg/kg/day) vs. (B) 4 weeks of ribavirin dosing before initiation of PEG-interferon dosing (“priming”, ≥13 mg/kg/day) followed by concentration targeted (≥ 2.5 mg/L (10.25 μmol/L) 28 days after initiation of ribavirin therapy) dosing of ribavirin in combination with peginterferon alpha-2a in interferon naïve patients with chronic hepatitis C (CHC) virus genotype 1 infection as compared to (C) standard-of-care dosing of ribavirin (≥13 mg/kg/day without monitoring of ribavirin concentrations) in combination with peginterferon alpha-2a as evaluated by the early viral kinetic response and SVR measured by effect on the initial decline of HCV-RNA (during the first days after initiating peginterferon and ribavirin therapy) and second phase decline (day 7 to week 12 of therapy).

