## early virological response

## pharmacokinetic response to ribavirin

# STUDY MEDICATIONS

## Dose and Schedule of Study Medications

Patients will receive PEGASYS® 180 g in 0.5 mL (prefilled syringes) administered sc once weekly. Specific guidelines for adjusting the dose of PEGASYS® are provided in Section 8.3. All PEGASYS® administrations will be via the sc route utilizing sterile technique. Test drug may be self-administered by the patients, except for the first dose, which should be administered in the clinic under the supervision of study personnel. Before providing the patient with test medication, the investigator or a qualified staff member will instruct the patient on the proper methods of storage of the medication, self-injection, and management and disposal of needles and syringes.

Patients will in combination with PEGASYS receive COPEGUS (ribavirin) which is administered p.o. daily: 13 mg/kg body weight. In Group A, patients will receive COPEGUS (ribavirin) 26 mg/kg body weight for the first 2 weeks (“Loading”) followed by COPEGUS (ribavirin) 13 mg/kg body weight for the remaining treatment duration. In Group B, patients will receive monotherapy with COPEGUS (ribavirin) 13 mg/kg body weight for 4 weeks prior to initiation of PEGASYS combination therapy. In both Group A and B, a ribavirin concentration will be obtained at local lab on day 28 after the initiation of PEGASYS, allowing for dose adjustments as deemed fit by the treating physician with the goal of achieving a ribavirin concentration (≥ 2.5 mg/L or 10.25 μmol/L). In Group C all patients will receive COPEGUS (ribavirin) 13 mg/kg body weight in combination with PEGASYS for the entire treatment duration without a ribavirin concentration without assessment on day 28 (“Standard-of-Care”)

All patients in this study will receive ribavirin treatment with food. By definition, ribavirin, with food entails taking their doses within 1 hour before or 2 hours after a meal. The meal should be considered “regular” as opposed to “fat-restricted”. Dose adjustment guidelines for ribavirin are provided in section 8.3.

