## Preparation and Administration of Study Medication

PEGASYS will be supplied to patients in commercial packaging each containing four pre-filled syringes containing 180 µg/ml PEGASYS. Patients should be informed to keep syringes stored refrigerated at 2-8 Celsius out of reach of children.

Copegus will be supplied to patients in commercial packaging each containing 168 tablets of 200 mg Copegus or 56 tablets of 400 mg . Patients should be informed to keep tablets stored at room temperature (15-30 Celsius) out of reach of children. Ribavirin should be administered twice-daily with food.

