Appendix 5 Instructions for Sample Processing and Shipment for RibaC:

**Please note that all samples should be collected using PPT VacutainerâTube before the morning dose of ribavirin because we will be monitoring ribavirin concentrations throughout the study!**

1. **Virology: HCV-RNA (screening visit, day 0 (just prior to the 1st dose of pegylated interferon; day 0 is the day that the first dose of the study medication is given), day 3, day 7 (before the 2nd dose of pegylated interferon), day 28 (before the 5th dose of pegylated interferon), week 12, End of Treatment, Follow-Up week 24)**

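### Appendix 3 gives the Group A loading dose three times daily over day 0 to day 14, but the body says ribavirin is given twice daily and loading lasts 14 days; the two must be reconciled

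*Protocol*

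**What the plan says.** **Frequency.** In Appendix 3, the asterisk on the Group A loading column leads to the footnote "Dose given TID". Section 7.2 says "Ribavirin should be administered twice-daily with food". The same instruction appears in section 1.4.4.2, at the end of the paragraph that introduces the Group A double dose, and in section 8.3.2. None of the three exempts the loading phase. Section 7.1, which sets out dose and schedule, gives the loading dose without a number of intakes per day.

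**Duration.** The Appendix 3 loading column is headed "Ribavirin dose day 0 – day 14", and the next column, with the lower dose, begins "Ribavirin dose day 15". Section 2.1 describes loading as "≥26 mg/kg/day for 14 days followed by ≥13 mg/kg/day", as does the synopsis under Objectives. Section 7.1 has "26 mg/kg body weight for the first 2 weeks". Sections 1.4.4.2 and 3.1 and the synopsis description of Group A also say 2 weeks. Appendix 5, in the virology item, states that "day 0 is the day that the first dose of the study medication is given".

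**Amount.** The first row of the Appendix 3 table reads "45-60 kg | 1600 mg | 800 mg". Neither dose column says whether its figures are per day or per intake.

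**The concern.** Loading is one of the two experimental regimens. Its purpose (section 1.4.1) is to reach higher ribavirin concentrations early. A site that doses from Appendix 3 and a site that doses from section 7.2 would use a different number of intakes per day. They could also disagree on whether day 14 is a loading day.

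The stake is uniform treatment and clear instructions in an arm given a doubled dose. The missing per-day label is part of this, because the figures stand beside a footnote saying the dose is given three times daily. Early ribavirin troughs and the day 0 to 3 HCV-RNA decline are measured during loading, so the regimen behind the comparison of Group A with Group C should be described in one way only.

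**Working it through.** **1. Does the table reproduce the stated daily dose?** Inputs are the Appendix 3 loading doses and weight bands. The formula is dose divided by body weight, treating the figure as a daily total.

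| Band (kg) | Loading dose (mg) | mg/kg at top of band | mg/kg at bottom of band |
|---|---|---|---|
| 45-60 | 1600 | 26.67 | 35.56 |
| 61-75 | 2000 | 26.67 | 32.79 |
| 76-90 | 2400 | 26.67 | 31.58 |
| 91-105 | 2800 | 26.67 | 30.77 |

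Every band meets the body's minimum of 26 mg/kg/day, and each loading dose is twice the dose in the next column. The amount agrees between body and appendix when the figures are mg per day.

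**2. What if the figures were per intake?** At 60 kg, 3 × 1600 = 4800 mg/day, and 4800/60 = 80 mg/kg/day. The body's minimum alone does not exclude this, since 80 exceeds 26. Section 7.1, which states 26 mg/kg without a minimum sign, and section 1.4.4.2, which calls it a double dose on a base of 13 mg/kg, do exclude it. The daily-total reading is the only one that fits the body, but it has to be found by cross-checking.

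**3. Does the 14-day duration reproduce?** Day 0 is a dosing day (Appendix 5) and day 15 is the first day at the lower dose (Appendix 3). Days 0 to 14 inclusive are 14 − 0 + 1 = 15 days. The body says 14, so the duration does not reproduce.

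**4. How large is the extra day?** Let D be the daily loading dose. The disputed day would otherwise be given at D/2.

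- Appendix 3 over the first 15 days: 15 × D
- Body over the same 15 days: 14 × D + D/2 = 14.5 × D
- Ratio: 15/14.5 = 1.0345, or about 3.4% more, the same in every band
- At 45-60 kg: 15 × 1600 = 24,000 mg against 14 × 1600 + 800 = 23,200 mg

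This assumes that day 0 is a full dosing day. If it is only a partial day, the excess is smaller.

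**5. Which measurements can the extra day touch?** It is day 14 itself. That is after the day 0 to 3 decline used in the sample-size section and after the day 1, 3 and 7 troughs. It lies inside the day 7 to 28 decline and before the day 28 concentration.

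**6. Frequency and troughs.** The documents give no pharmacokinetic parameters. Section 1.4.1 says steady state takes more than 4 weeks (672 h). Assuming one-compartment decay and 4 to 5 half-lives to steady state, the half-life is at least 672/5 = 134 h to 672/4 = 168 h. Over the 4 h between an 8 h and a 12 h interval, a level then falls by at most 1 − 2^(−4/134) ≈ 2%. An early distribution phase could make day 1 differ more; the documents do not allow that to be calculated.

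**The case against.** The strongest reply is that the specific rule overrides the general one. The asterisk attaches to the Group A loading column only, the next column carries a different mark, and the Group B and C table has no such footnote. The twice-daily sentence is generic: section 7.2 is mostly about packaging and storage, and section 8.3.2 mainly concerns later dose changes. A site using Appendix 3, the only place that turns mg/kg into weight-band doses, meets the footnote directly below the table. Patients also record each Copegus dose in a diary (section 7.4), so actual practice could partly be recovered.

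Much of this stands. The exception reading is plausible, and section 8.3.2 is weak evidence about loading. But no sentence states the exception, and in section 1.4.4.2 the twice-daily sentence closes the very paragraph that introduces the double dose. The reply also does not address the day count.

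A reader might infer more than the documents support:

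- **That the loading regimen as a whole is undefined.** The daily amount is consistent; only the frequency and the last loading day are open.
- **That early troughs would mix two clearly different exposures.** The documents do not quantify this, three intakes with food need not mean an 8 h overnight gap, and the long half-life suggests a small effect.
- **That totals which do not divide equally into three intakes of tablets reveal an error.** Equal intakes are never required, and at 200 mg per tablet the 1000 mg and 1400 mg doses (5 and 7 tablets) already split unequally when given twice daily.
- **That the extra day adds a fourteenth to exposure.** That ignores the standard dose the patient would receive on that day anyway.

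**Conclusion.** The protocol contradicts itself on two features of the Group A loading phase: intakes per day (three in Appendix 3, two in the body) and length (15 days by the Appendix 3 window, 14 days or 2 weeks in the body). The second rests on day 0 being a full dosing day. The definition of day 0 comes from a sampling instruction and does not fit Group B, whose first ribavirin dose is on day -28, but it does apply to Group A.

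The size is modest: about 3.4% more ribavirin over the first 15 days, with the total daily dose in agreement. Sample size, alpha and power do not change. Any effect of frequency on troughs is unquantified and probably small. The point still deserves correction, because these are dosing instructions for an experimental arm and the table is unlabelled as to per day or per intake next to a three-times-daily footnote. Which frequency and which last loading day are right is for the sponsor to settle.

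**What to change.** - Reconcile Appendix 3 with sections 1.4.4.2, 7.2 and 8.3.2 on the number of intakes per day during loading. If the footnote is a deliberate exception for the loading phase, say so where the general rule is stated.
- Reconcile Appendix 3 with the synopsis (Objectives and Group A description) and sections 1.4.4.2, 2.1, 3.1 and 7.1 on the last loading day, counted from day 0 as the protocol defines it.
- Label the Appendix 3 figures as daily totals if that is what is meant.

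The cost is protocol wording and a note to sites. No design, sample-size or analysis change is needed.
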